### 2.2. Recruitment and Screening of Participants

Participants in this study will be selected by the treating neurologists. Subsequently, they will be contacted via telephone by the researchers. All patients will be informed about the purposes of the research and will have to sign an informed consent before undergoing any type of evaluation. Patients who will meet the inclusion criteria will be assigned to one of the three rehabilitation conditions using a stratified randomized sampling strategy in order to control variables such as disease course or sex, which could make the groups not comparable. The inclusion and exclusion criteria are summarized in Table 1.

### 2.3. Assessment Procedures

At T0 all patients will undergo the following assessments:Accurate collection of personal, anamnestic and clinical information;Expanded Disability Status Scale (EDSS) [24]: is a rating scale administered by a trained physician, aimed at evaluating functional CNS sub-systems. EDSS is used also to identify disease progression in MS patients and to evaluate the effectiveness of therapeutic interventions in clinical trials. It consists of an ordinal classification system ranging from 0 (normal neurological status) to 10 (death for MS) in increments of 0.5 (when EDSS 1 is reached). The lower values of the EDSS scale measure deficits based on neurological examination, while the upper range of the scale (>EDSS 6) measures the handicaps of MS patients [25]. The determination of the 4–6 interval of the EDSS strongly depends on aspects concerning walking [25].Neuropsychological evaluation through the Minimal Assessment of Cognitive Functioning in Multiple Sclerosis battery (MACFIMS) [26], in the Italian version [27]. This battery consists of seven tests:
○The California Verbal Learning Test-II (measurement of verbal learning and memory; CVLT-II) [28,29] requires the learning of a 16 words list (made up of 4 words from four different categories) read by the examiner across five trials. After each trial the subject has to recall as many words as possible in any order; the number of words correctly recalled for each trial is recorded. The total Immediate Recall (IR) score is the sum of the words correctly recalled across the five trials, ranging from 0 to 80. After having performed some interference tests the patient has to repeat the previously learned words (Delayed Recall; DR).○The Brief Visuospatial Memory Test—Revised (visuospatial memory test; BVMT-R) [30] consists of three consecutive trials in which the subject views for 10 s a display of six non-iconic figures, arranged in a 2 × 3 matrix. After that the subject has to reproduce each figure in the correct locations on the page. Patient is asked to reproduce the figures again after a 25-min interval without any further exposure to the stimuli. Scoring is based on the subject’s reproduction accuracy and location of each figure [31]. Each figure reproduced can receive 0 to 2 points score [32]. The Immediate Recall (IR) corresponded to the scores’ sum obtained across the three trials while the Delayed Recall (DR) is the score obtained in the 25-min delayed trial. The BVMT-R offers six equivalent alternative forms [33].○The Symbol Digit Modalities Test (information processing speed; SDMT; oral version) features a series of nine symbols, each of which is paired with a single-digit number in a pattern at the top of a sheet. The rest of the page has a pseudo-randomized sequence of these symbols. The patient is asked to say the digit associated with each symbol as quickly as possible in 90 s. The SDMT was originally designed for both written or oral responses, but the expert group recommended oral administration with MS patients to minimize complaints due to upper limb weakness or incoordination. The dependent variable is the total number of correct answers in 90 s [33,34].○The Benton Judgment of Line Orientation test (measures the accuracy of spatial orientation judgments; BJLO) [35] requires subjects to identify the angle defined by two stimulus lines among those reported in a visual series of lines spanning 180 degrees. The dependent variable of the BJLO is the total number of correct answers [33].○The Controlled Oral Word Association Test (measure of phonemic fluency; COWAT) gives subjects three 1-min time intervals each to generate as many words as possible beginning with three different input letters. Given that the subject’s performance is strongly influenced by the efficiency and speed of the search into one’s own lexicon, the COWAT cannot be considered a test of “pure” language. The total score is the total number of words generated in all three tests. Two equivalent alternative forms are available [33].○The Delis–Kaplan Executive Function System Sorting Test (D-KEFS ST) is a composite measure of: concept formation skills, specific problem-solving skills for verbal/non-verbal aspects and ability to explain the abstract ordering of concepts [36]. It is able to explore reasoning, categorization skills, problem solving, abstraction, flexibility of thought and conceptual training skills, and it also provides good validity [37] and adequate reliability [38]. The test involves the presentation of six mixed cardstocks having different perceptual and semantic characteristics. The participant is asked to divide the cards into two groups (categorization), with three cards each, based on objective criteria and to describe the concepts used to generate each categorization (description). Each of the two sets of cards has a maximum of eight types of categories: three based on the semantic meaning of the printed words and five based on the cards’ visuo-spatial characteristics or patterns. The participant has a maximum of 4 min (for each set of cards) to find as many categorizations as possible [39]. The Sorting Score (SS) represents the total number of correct categorizations made by the subject; the Point Score (PS) represents the quality of the description (classifications) made for all the SS.○The Paced Auditory Serial Addition Test in 3 and 2 s versions (measure of working memory; PASAT). It takes 20 min to administer and has adequate sensitivity and specificity (approximately 75% and 90%, respectively) in discriminating compromised patients from intact ones [40,41] In this test the patients asks some digit numbers each 3 or 2 s. He/she is asked to sum the number just said with the previous and say each time the correct sum.

The Beck Depression Inventory (BDI) [42] is a self-report tool that allows you to assess the severity of depression in patients of at least 13 years of age. The test consists of 13 items with a score ranging from 0 to 3 from which a total score is derived. The test was developed as an indicator of the presence and intensity of depressive symptoms at the time of administration. It is useful in assessing depressive mood changes, estimating suicide risk and correctly assessing depressive symptoms in primary prevention, intervention and follow-up.The State–Trait Anxiety Inventory Y form (STAI Y) [43] is made up of two subtests of 20 items each with a 4-level response scale of intensity (e.g., from “almost never” to “almost always”). The first subtest evaluates how subjects feel at the time of testing, the second focuses on how subjects generally feel. The two scales refer, respectively, to state anxiety (considered a temporary interruption of the emotional continuum), conceived as a particular experience, a feeling of insecurity, of helplessness in the face of a perceived damage that can lead either to worry or to escape and avoidance; and trait anxiety (considered a relatively stable personality characteristic or a behavioral attitude) which reflects the tendency to perceive stimuli and environmental situations as dangerous or threatening [44].The World Health Organization—Disability Assessment Schedule (WHO-DAS 2—Disability level assessment questionnaire) is a tool developed by the WHO in 1998 in order to evaluate the limitations of activities and restrictions on participation experienced by a patient due to its medical condition. The WHODAS-2 is made up of 36 items that evaluate the functioning and the disability of the subject in a time window of 30 days [45]. The questionnaire covers 6 domains: cognitive functions (6 items), mobility (5 items), self-care (4 items), interaction with others (5 items), daily life activities [domestic activities (4 items), work/school (4 items)], participation in social life (8 items). The answer options range from 0 (no difficulty) to 5 (total difficulty) [46].The Multiple Sclerosis Neuropsychological Questionnaire (MSNQ) [47] is a brief self-administered test with 15 questions that reflect neuropsychological competence during activities of daily living. Each item is rated on a 5-point Likert scale, which goes from 0 (never, never happens) to four (very often, very seriously). A total score is obtained from the sum of the points of each single item.The Multiple Sclerosis Functional Composite (MSFC) is a functional assessment consisting of three tests:
1.The Timed 25 Foot Walk (T25FW) is a quantitative measure of the function of the lower limbs. The patient is directed to the end of a clearly indicated path and is asked to walk 7.62 m as quickly as possible, but safely. The activity is immediately repeated making the patient return to the initial starting point. If necessary, patients can use an assistive device during the test. Three scores are obtained: two relating to single walks and one given by the averaged time of the two paths [48].2.The Nine Hole Peg Test (NHPT) is a simple and relatively quick evidence-based test that measures the functions of the upper limbs (hand and arm) [49]. It consists of a standardized test apparatus consisting of a platform with nine holes and nine pegs to insert. Participants are seated and then asked to insert and then remove the nine pegs from the nine holes, one at a time, as quickly as possible. Both dominant and non-dominant hands are tested twice (two consecutive dominant hand trials, immediately followed by two consecutive non-dominant hand trials) [48]. At the end of the test, 6 scores are obtained: 2 relating to the time taken to perform the task with the dominant hand, 2 scores relating to the time spent with the non-dominant hand and finally two scores representing the average time taken to perform the test with the dominant and the non-dominant hands.3.The PASAT (see on the previous page).The Six Minutes Walking Test (6MWT) is a test developed by Balke in 1963 [50], as an index of motor resistance [51]. The test requires the subject to walk for 6 min without interruption, following a path marked by the therapist through the aid of cones that delineate the boundaries. The subject is allowed to rest when necessary [50]. The distance traveled is measured in meters by a special tool: the measuring wheel.The Tinetti Scale (TS) is a clinical tool that allows the assessment of patient’s balance and walking performance by assigning an objective score to the motor performance. The Tinetti scale is composed of a section that evaluates static balance, characterized by 9 items with a global score between 0 and 16, and a section that evaluates gait, composed of 7 items with a global score between 0 and 12. Both sections can be scored by the examiner on a 3-point ordinal scale (0 = inability to execute the request; 1 = ability to execute with adaptations or aids; 2 = ability to execute it without adaptation) or 2-point ordinal scale (0 = inability to execute the request; 1 = ability to execute it without adaptation). The patient can obtain a total score between 0 and 28. Thanks to the obtained score, the examiner is able to quantify the risk of falling and has a basis on which to develop personalized rehabilitation programs [52].The Berg Balance Scale (BBS) is one of the most common clinical measures of static and dynamic balance [53]. The BBS includes 14 items that assess a person’s ability to maintain balance while performing activities of different difficulty (e.g., going from sitting to standing, picking up an object from the floor, turning 360°). A score is assigned to each item on a 4-point ordinal scale from 0 (=unable to perform) to 4 (=normal performance), accounting for the patient’s ability in performing the exercises without any aid. The BBS has a strong inter-rater and test–retest reliability [54].

### 2.4. Randomization

After having completed the assessment procedures, the participants will be randomized to the three rehabilitation arms. The randomization assignment will foresee a stratification by age groups (<30; 30–40; 41–50; 51–65; >65) and will be weighted with respect to the variable phenotype of pathology (each group will be guaranteed a distribution of patients in RR or SP course representative of the incidence of the two courses in the Italian MS population) [55]. This will be a single-blind study.

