## Abstract

MS clinical features vary between patients. In approximately 60% of cases, cognitive deficits are associated with motor disabilities, with consequences on both walking and maintaining balance and cognitive efficiency. Multimodal programs are very infrequent for MS patients and cognitive rehabilitation is not provided by the Italian health system, which only favors access to motor rehabilitation. Dual-task studies showed how motor and cognitive skills are closely associated. Therefore, physiotherapy exercises may favor an indirect improvement in cognition. The aim of this study is to understand which rehabilitative approach may increase both cognitive and motor efficiency, avoiding the waste of time and resources. In this multi-site single-blind parallel controlled clinical trial, we will compare three rehabilitative approaches: cognitive training, motor training and combined cognitive–motor training. We also aim to evaluate: whether self-perception and objective improvement correspond; the impact of each rehabilitation program on patients’ QoL, mood and self-perception; and long-term effects. A total of 60 patients will be randomly assigned to one of the three treatments for two 45-min sessions/week for 12 weeks. All participants will undergo a complete cognitive, motor, clinical assessment together with mood, self-perception, and QoL questionnaires before, immediately after and 6 months after the training period.

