## 2. Materials and Methods

### 2.1. Aim, Design and Setting of This Study

This study has the following primary objectives:Compare three forms of rehabilitation—cognitive, motor and combined (cognitive–motor)—in three groups of MS patients.Check whether a combined rehabilitation approach can induce a significantly greater improvement on memory efficiency of MS patients, than cognitive rehabilitation performed alone.

Secondary objectives:Evaluate whether self-perception and objective improvement correspond.Evaluate the impact of each rehabilitation program on patients’ overall disability.Monitor the effects of the three rehabilitation conditions after 6 months.

This study will be a single-blind parallel controlled clinical trial, in which each subject will be randomly assigned to a single treatment. The study protocol will be divided into an initial evaluation by standardized tools of clinical, cognitive, emotional, quality of life and functional self-perception state, at time 0 (T0). Subsequently, patients will be assigned to one of the three conditions and will undergo rehabilitation treatment for a total of 12 weeks (two sessions each week). At the end of the treatment, each patient will undergo an overall re-evaluation (T1) with parallel forms of the tools used at T0. After 6 months, all patients will be submitted to a further overall re-evaluation as a follow-up measurement of each treatment (T2). The examiner carrying out pre- and post-treatment evaluations will be different from the one carrying out the rehabilitation process in order to avoid any individual bias. Figure 1 shows the study flowchart.

Patients in charge of both the “Santa Lucia” Neuroscience and Rehabilitation Foundation (Rome) and the “Filippo Turati” Foundation (Rome) will be recruited. All evaluations and rehabilitation training will be conducted at the laboratory and in the rehabilitation sites of the two centers by adequately trained neurologists/physiatrists, psychologists and physiotherapists.

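### Sections 2.2 and 2.4 name only partly matching stratification factors, one age band is unreachable, and the between-group ANOVAs include none of the factors, which costs some power but not validity

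*Protocol article*

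**What the plan says.** Two sections of the protocol article describe how patients are assigned.

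- Section 2.2 says eligible patients are assigned "using a stratified randomized sampling strategy in order to control variables such as disease course or sex".
- Section 2.4 says: "The randomization assignment will foresee a stratification by age groups (<30; 30–40; 41–50; 51–65; >65"). It adds that the assignment "will be weighted with respect to the variable phenotype of pathology", so that "each group will be guaranteed a distribution of patients in RR or SP course representative of the incidence of the two courses"; the reference for that mix is MS in Italy.

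Table 1 limits age at entry to 18–65 years and phenotype to RRMS or SPMS.

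The abstract calls the study a "multi-site single-blind parallel controlled clinical trial". Section 2.1 says evaluations and training "will be conducted at the laboratory and in the rehabilitation sites of the two centers". Neither section on assignment names centre.

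Section 4.1 plans two analyses of the cognitive scores: a repeated measures ANOVA over T0, T1 and T2 within each group, and an ANOVA comparing the groups at T0, T1 and T2. The same is planned for mood, self-perception and perceived disability. No term for age, disease course, sex or centre is named. The sample size (48, raised to 60) is derived for a within–between interaction.

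**The concern.** Whoever builds the allocation list needs one set of factors, and the article gives two that overlap only in disease course. Sex is one of just two variables that section 2.2 names as a threat to comparability, yet it is absent from the section that fixes the scheme. Age has the reverse position. The band above 65 conflicts with Table 1. The phenotype clause promises agreement with an external proportion, which depends on who is recruited and not on how recruits are allocated.

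The second issue is the link to the analysis. Stratified allocation makes the arms more alike on age and course than chance would. An ANOVA that ignores those factors keeps their variance in the error term, so its p-values are too large on average and some power is given away. Any difference in level between the two centres also stays in the error term.

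**Working it through.** **1. The passages side by side**

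| Factor | Section 2.2 | Section 2.4 | Section 4.1 model |
|---|---|---|---|
| Disease course / phenotype | yes (example) | yes (weighted) | not named |
| Sex | yes (example) | no | not named |
| Age | no | yes (5 bands) | not named |
| Centre | no | no | not named |

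Five age bands are listed. Entry at 18–65 reaches the first four only, since the band 51–65 already covers the upper limit. Four bands by two courses give at most 8 cells, an average of 60/8 = 7.5 patients per cell.

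**2. The plan's own sample size**

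Inputs from section 4.1: f = 0.30, alpha 0.05, power above 0.95, 3 groups. Assumed, because not stated: correlation 0.5, sphericity, m = 2 measurements.

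The noncentrality is f² × N × m / (1 − rho), with (k − 1)(m − 1) and (N − k)(m − 1) degrees of freedom.

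- N = 48: 0.09 × 48 × 2 / 0.5 = 17.28, F(2, 45), power 0.958.
- N = 45: 0.09 × 45 × 2 / 0.5 = 16.2, F(2, 42), power 0.945.

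So 48 is reproduced. With three measurements the minimum would be 39 (power 0.962). The calculation concerns the interaction and contains no stratification factor, so this point does not change the stated N.

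**3. The between-group ANOVA at one visit**

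The setting was simulated with N = 60, three arms, and permuted blocks of 3 within 4 age bands × 2 courses, 4,000 runs per setting. Assumed: age-band shares 20/30/30/20%, RR/SP 85/15%, a score that depends additively on age band and course, and a share R² of the within-arm variance explained by them. For f = 0.30 the arm means were −d, 0 and +d with d = 0.30/√(2/3) = 0.367. The adjusted model adds age band (3 df) and course (1 df).

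| Assumed R² | Alpha, factors omitted | Alpha, factors included | Power, omitted | Power, included |
|---|---|---|---|---|
| 0 | 0.053 | 0.051 | 0.52 | 0.52 |
| 0.1 | 0.043 | 0.056 | 0.50 | 0.55 |
| 0.2 | 0.030 | 0.048 | 0.50 | 0.61 |
| 0.3 | 0.015 | 0.051 | 0.48 | 0.67 |

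The simulation standard error is about √(0.05 × 0.95/4000) = 0.003 for alpha and √(0.5 × 0.5/4000) = 0.008 for power. The adjusted alphas are therefore compatible with 0.05.

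*Cross-check.* If allocation balanced the factors perfectly, the unadjusted F statistic under the null would be about (1 − R²) times an F(2, 57) variable. The critical value is 3.159, and P(F > x) = (1 + 2x/57)^(−28.5).

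- R² = 0.1: x = 3.159/0.9 = 3.51, probability 0.037.
- R² = 0.2: x = 3.159/0.8 = 3.95, probability 0.025.

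The simulated 0.043 and 0.030 lie between these limits and 0.05, as expected with good but imperfect balance.

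**4. Whether 8 cells balance the arms**

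Under the same blocks and age-band shares, with an RR share of 50–85%, the mean difference between the largest and smallest SP count across arms is about 1.5 patients. Without stratification it is 2.6 to 3.8. The between-arm variance of age band falls by about 90%. The stated scheme does balance the arms.

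**5. The group-by-time interaction**

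A stable patient factor that adds the same amount at every visit drops out of each patient's change from T0. The loss in step 3 therefore concerns the comparisons at single visits.

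**The case against.** The strongest case on the other side is that only wording is at stake. Section 2.2 offers its variables as examples, disease course is in both sections, and an empty age band harms nothing. The article condenses a fuller protocol, and an analysis plan not shown may add the covariates. If recruitment were representative, stratifying by course would give each arm roughly the national mix.

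Much of this stands. The mismatch is partial, limited to sex and age. The empty band does not affect validity. The phenotype clause is loose wording rather than an unworkable design, although section 2.2 describes selection by treating neurologists and states no quota, so nothing in the text secures the national mix. The model point is the weakest part on its own: section 4.1 does not rule covariates out. It remains worth making because the section does set out the between-group analysis, and adding the factors is almost free.

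Three stronger readings are tempting and not supported:

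- *A reader might infer that so many small strata cannot balance 60 patients.* Step 4 of the working shows that the 8 reachable cells do, and the conservatism in step 3 arises precisely because they do. Larger cell counts would require factors that section 2.4 does not cross.
- *A reader might infer that centre must be a stratification factor because staff differ by site.* The article says only that trained staff work at both centres; a difference in staff is an inference. Replacing age by centre as a stratifier would be a preference.
- *A reader might infer that omitting the factors inflates false positives or undermines the sample size.* The error runs the other way, and the sample size rests on the interaction.

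**Conclusion.** The point holds as an inconsistency to be reconciled and a modest, avoidable loss of efficiency. Sections 2.2 and 2.4 disagree on sex and age, section 2.4 and Table 1 disagree on patients above 65, and the guaranteed national RR/SP mix is not something allocation can deliver.

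For the between-group ANOVA at a single visit, leaving out the factors gives a true alpha of about 0.043 to 0.030 instead of 0.05. Power is 0.50 instead of 0.55 to 0.61, a loss of about 5 to 11 percentage points. These figures rest on N = 60, f = 0.30, blocks of 3, the assumed stratum shares and an assumed R² of 0.1 to 0.2; the documents give none of the last three. If the factors explain nothing, nothing is lost. Validity is not harmed, and the group-by-time interaction is largely unaffected as long as the factors act equally at all visits.

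**What to change.** 1. State one list of stratification factors, identical in sections 2.2 and 2.4, and say whether sex is on it.
2. Reconcile the age bands with Table 1 so that every band listed can be reached.
3. Reword the phenotype clause as balance of RR and SP between the arms. If a national mix is wanted, describe it as a recruitment target.
4. In section 4.1, enter the factors actually used in allocation in every between-group model: age as a continuous covariate, disease course, and sex if used. Add centre as a covariate.

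The cost is a text correction and a few degrees of freedom: four for age, course, sex and centre at one each, leaving 57 − 4 = 53 error degrees of freedom with 60 patients at a single visit. If enrolment has begun, the allocation list can stay as it is. The article should then report the factors actually used, and the model change remains available.
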